#### **Data management**

Baseline data will be collected on paper by the local research nurses. Forms will be copied, with originals stored locally and copies transferred securely in tamper-proof envelopes to the trials unit for entry into the database. Staff at the trials unit will mail or email out the follow up patient questionnaires, according to the participant's stated preference, and enter the returned questionnaires into the database. Study data will be collected and managed using REDCap hosted at the University of Bristol. The database incorporates data entry and validation rules to reduce data entry errors, and management functions to facilitate auditing and data quality assurance.

Identifiable information, as agreed with partner organisations and set out in the participant information sheet, will be used to link this primary dataset with existing routine healthcare data bases for follow up. The flow of data – identifiable and pseudonymized – is summarized in **Figure 2**. The database system will protect patient information in line with the data protection legislation and any specific requirements of the partner organisations. Trial staff will ensure that participants' anonymity is maintained through

protective and secure handling and storage of patient information. The chief investigator (CI) will act as custodian of the full dataset.

[figure not shown]

## 7.7 Nested studies: QuinteT recruitment intervention

The QuinteT Recruitment Intervention (QRI) (34) will be integrated throughout the H4RT recruitment period, with the aim of optimising recruitment and informed consent. Recruitment may be challenging if clinicians, nurses, or patients have strong preferences for HD or HDF. There may also be unforeseen logistical challenges to randomising patients to a treatment (HDF) that is not yet fully integrated into clinical practice in some centres. The QRI assimilates investigation of generic and centre-specific recruitment challenges, with a combination of pre-emptive and responsive feedback/training.

The QRI will attempt to identify sources of recruitment difficulties as they occur and implement generic or bespoke strategies to address these. Recruitment processes will be investigated in depth across a

small number of clinical centres (i.e. 3 or 4) in the early phases of recruitment, with reviews of other centres as they open and recruitment proceeds. There will be an attempt to ensure these initial centres are as diverse as possible (e.g. in terms of size, current use of HDF, etc.). Lessons learnt from the QRI will subsequently be applied to other centres, combined with continued investigation of recruitment challenges.

The QRI uses novel qualitative and mixed-method approaches pioneered during the NIHR HTA-funded ProtecT (Prostate testing for cancer and Treatment) study (35). These methods have since been refined and applied to several other RCTs in different clinical contexts, all of which have led to insights about recruitment issues (36-38) and the development of recruitment strategies (34, 39). The QRI will proceed in two iterative phases: sources of recruitment difficulties are rapidly investigated in Phase I, informing a mix of generic and tailored interventions to improve recruitment in phase II.

### **7.7.1 PHASE I: understanding recruitment**

Phase I aims to understand the recruitment process and how this operates in clinical centres. A multi-faceted, flexible approach will be used to investigate site-specific or wider recruitment obstacles. These will comprise one or more of the following methods of data collection:

#### ***a) In-depth interviews***

Semi-structured interviews will be undertaken with three groups: (i) members of the Trial Management Group (TMG), (ii) clinicians or researchers who are involved in trial recruitment ('recruiters'), and (iii) eligible patients who have been approached to take part in the trial. Interviews with members of the TMG and recruiters will explore their perspectives on the RCT and experiences of recruitment. Key topics explored will include: perspectives on the trial design; views about the evidence on which the trial is based; perceptions of equipoise; perceived barriers and facilitators to recruitment; integration of the trial in clinical centres, and any difficulties in implementing the trial protocol. Interviews with patients will explore views on the presentation of study information, understandings of trial processes (e.g. randomisation), and reasons underlying decisions to accept or decline the trial. Patients will be purposefully selected, to build a sample of maximum variation based on the centre/clinic they attend, their final decision about trial participation (i.e. accept or decline), and any other clinical (or non-clinical) characteristics that are deemed to potentially have a bearing on their decisions about trial participation. Some of these characteristics will likely emerge from interviews with clinical professionals. Numbers of interviews for each group of informants will be guided by the concept of 'data saturation' – the need to continue sampling until no new themes emerge. All interviews will be audio recorded on an encrypted device, and take place at a mutually convenient location, in a suitably private and quiet setting. All participants will be offered the option to conduct the interview over the telephone. The University of Bristol's 'lone researcher'

safety policies will be upheld for any interviews taking place in non-public settings (e.g. participants' homes).

***b) Audio-recording recruitment discussions***

Scheduled appointments during which the H4RT is discussed with patients, including telephone conversations, will be audio-recorded on an encrypted device (and potentially observed) with written informed consent. These recordings/observations will be used to explore information provision, recruitment techniques, management of patient treatment preferences, and reasons underlying trial-participation decisions. Recording/observing appointments will also enable comparison of reported and actual recruitment practices for recruiters have also participated in interviews. Recordings will be collected by trial staff across the clinical centres, and transferred to and from the University of Bristol through University of Bristol-approved secure data transfer facilities or encrypted flash drives that adhere to NHS Trust policies.

***c) Mapping of eligibility and recruitment pathways***

Detailed eligibility and recruitment pathways will be compiled for clinical centres, noting the point at which patients receive information about the trial, which members of the clinical team they meet, and the timing and frequency of appointments. Recruitment pathways will be compared with details specified in the trial protocol and pathways from other centres to identify practices that are potentially more or less efficient. The QRI researcher will also work closely with the clinical trials unit (CTU) to compose detailed logs of potential participants as they proceed through screening and eligibility phases. This will help to identify points at which patients do not continue with recruitment to the RCT, thus indicating aspects of the recruitment process that may warrant further investigation and/or intervention.

Logs of eligible and recruited patients will be assembled using simple flow charts and counts to display numbers and percentages of patients at each stage of the eligibility and recruitment processes. These figures will be compared across centres, and considered in relation to estimates specified in the grant application/study protocol.

***d) Observation of TMG and investigator meetings***

The QRI researcher will regularly observe TMG meetings to gain an overview of trial conduct and overarching challenges (logistical issues, etc.). These meetings may be audio-recorded, subject to written informed consent.

## **7.7.2 PHASE 2: Development and implementation of recruitment intervention strategies**

If recruitment difficulties are evident across the study or in particular centres, the QRI team will work closely with the TMG/CI to formulate a 'plan of action' that intends to improve recruitment and information provision. The components of this plan will be grounded in the findings from

phase 1, and may include generic, centre-specific, or individually-targeted interventions. Generic forms may include 'tips' documents that provide suggestions on how to explain trial design and processes, or changes to trial documentation and trial processes. Supportive feedback is likely to be a core component of the plan of action, with the exact nature and timing of feedback dependent on the issues that arise. Centre-specific feedback may cover institutional barriers, while multi-centre group feedback sessions may address widespread challenges that would benefit from discussion. All group feedback sessions will be aided by displaying anonymised data extracts from interviews and audio-recorded consultations. Individual confidential feedback will also be offered – particularly where recruiters experience specific difficulties, or where there is a need to discuss potentially sensitive issues. Investigator meetings/teleconferences and site visits from the CI/TMG members may also be employed to discuss technical or clinical challenges related to the trial (e.g. discomfort surrounding eligibility criteria).

### **7.7.3. Iterative nature of Phase I/Phase II**

The QRI has been presented as two distinct phases for clarity, although in reality these are likely to overlap. For instance, new avenues of enquiry will emerge throughout the conduct of the QRI (e.g. in feedback meetings), and rigorous monitoring of screening logs before/after interventions may indicate a need for further investigations (phase I) or intervention (phase II).

### **7.7.4. Evaluating the 'plan of action'**

The impact of QRI interventions implemented in phase 2 will be evaluated through mixed approaches, including 'before/after' comparisons (number of recruited patients, eligible patients identified, patients accepting allocation) and investigation of changes in recruiter practice (through continued analysis of audio-recorded appointments). Semi-structured interviews will be conducted with recruiting staff and TMG members to explore their views on QRI interventions and suggestions for areas that would benefit from continued QRI input.

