## **7 TRIAL PROCEDURES**

### **7.1 Recruitment, screening and consent**

Dialysis is provided by renal units, either in a main dialysis unit (with a nephrologist on site) or in a satellite dialysis unit (without a nephrologist on site). For adult patients, there are 71 main dialysis units and ~164 satellite dialysis units (235 units in total). Eligible patients will be dialysing three times a week in one of these units and each unit will know exactly who these patients are and when they will next be attending, with never more than 3 days between attendances. To optimise the efficiency of recruitment, potentially eligible patients will be approached according to their regular dialysis shift, thus enabling 2-3 patients to be recruited in a half-day/ single visit to a dialysis unit. These arrangements will be individualised according to local circumstances at each site. A patient recruitment poster in waiting areas of dialysis units may be used to signpost patients who are interested in taking part in the trial to a local contact who can provide further information.

Due to the COVID-19 pandemic, throughout the protocol: Face to face appointments must comply with local policies based on national guidance on social distancing and PPE; If clinically appropriate, patients can be approached by telephone/video call to minimise contact with the patient.

Identification, screening and consent procedures will be undertaken by research staff and treating clinicians who will be trained and competent to participate according to the ethically approved protocol, principles of Good Clinical Practice (GCP) and Declaration of Helsinki. It will take place in several steps:

1. Nurses in dialysis units will provide a list of potentially eligible patients in their units
2. Eligibility will be confirmed by the patient's treating clinician or the local principal investigator.
3. Standard letters will be sent out/ handed out to potentially eligible patients introducing the study and including a Patient Information Sheet.
4. Letters will be followed up with a phone call/ face-to-face visit from the research staff to offer further discussion about the study/a baseline visit at a scheduled dialysis attendance.
5. Potentially eligible patients will be approached according to their regular dialysis shift.

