#### **a) Quantitative evaluation**

Information about recruitment plans and targets specified in the trial documentation (protocols/funding application) will be recorded prior to the start of recruitment. This will include:

- The target recruitment figures (ideally for each centre, per month). If a target recruitment line has been provided as a figure (i.e. image), the raw data informing this line should be requested from the TMG or CTU overseeing the study. Where possible, the rationale behind these targets should be explored and recorded.
- The planned period of recruitment

- The planned number of centres

Recruitment data will be regularly collected (e.g. at least monthly) throughout the recruitment period. As a minimum, this will include the number of patients randomised per centre, per month. Ideally, the number of patients screened, eligible, and approached will also be routinely collected per centre, per month.

The timing of interventions stemming from the QRI should be recorded in the form of day/month/year, with a brief description of the activity. All activities should be recorded, including (but not restricted to):

- Feedback of 'phase 1' findings to the CI and/or TMG, including details of the agreed 'plan of action' (and any subsequent plans for intervention).
- 'Global interventions' (not specific to any particular centre – e.g. 'tips and guidance' documents, changes to PILs, early discussion of findings with the chief investigator)
- 'Centre-specific interventions' (e.g. individual or group feedback within a centre).

b) Qualitative evaluation:

Reflective interviews will be conducted with key informants once the collaboration with the QuinteT team is drawing to an end. Key informants will constitute any individuals who have been exposed to QRI interventions or had a role in delivering the QRI. This will likely include the CI, trial manager/coordinator, and recruiters who have received feedback/training.

Interviews will take place face to face or over the phone, and be informed by a flexible topic guide informed by previous work in this area (40). Ideally, interviews will be conducted by an independent member of the QuinteT team who has had no prior direct involvement in the RCT.

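### The before/after recruitment counts in section 7.7.4 can show a gain from centre-specific QRI action when there is none; a per-centre rate model on data already required would be better

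*Protocol*

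**What the plan says.** Protocol section 7.7.4 opens: "The impact of QRI interventions implemented in phase 2 will be evaluated through mixed approaches, including 'before/after" and continues "comparisons (number of recruited patients, eligible patients identified, patients accepting allocation". The same section adds "investigation of changes in recruiter practice (through continued analysis of audio-recorded appointments" and interviews with recruiting staff and trial management group members.

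Section 7.7.2 sets the trigger for a plan of action: "If recruitment difficulties are evident across the study or in particular centres, the QRI team will work closely with the TMG/CI". The action may be generic, specific to a centre, or aimed at an individual.

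Part a) of section 7.7.4 requires, as a minimum, numbers randomised per centre per month, and asks for interventions to be dated to the day. The denominators are softer: "Ideally, the number of patients screened, eligible, and approached will also be routinely collected per centre, per month".

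Conditions also change during recruitment, which runs from 01/11/2017 to 30/09/2022 (Trial Summary). The version table dates the waiting-area poster to 24 June 2020 and the COVID-19 changes to 15 July 2020. Section 7.1 carries the latter: "If clinically appropriate, patients can be approached by telephone/video call to minimise contact with the patient".

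**The concern.** Where a centre receives tailored help because its numbers are poor, the period before the help has been selected for being low. Part of any low count is chance, so the next period will on average be higher with no help at all. This is regression to the mean, and a before/after comparison in the same centre counts it as benefit.

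Other changes can fall between the two periods: more sites open, the pandemic, new ways of approaching patients. Section 7.7.4 names numbers rather than rates, and no concurrent comparison.

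What is at stake is the conclusion about the QRI. Section 9.2 anticipates that QRI lessons will help lift participation from 30% to 40%, and section 7.7 carries lessons from the first centres to the others. An overstated effect could direct that effort wrongly.

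**Working it through.** **1. The protocol's own recruitment figures.** Section 9.2 gives 4,104 eligible patients over 18 months, and 4,104 / 18 = 228 per month. At 30% for four months and 40% for two: 4 × 228 × 0.30 + 2 × 228 × 0.40 = 273.6 + 182.4 = 456. This is the six-month target in the progression table of section 9.6. It also equals 20 sites × 6 months × 3.8. The figures reproduce, so 3.8 per site-month is a fair base rate.

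**2. Chance variation in one centre.** If monthly counts are Poisson with mean 3.8:
- three months: mean 3 × 3.8 = 11.4, SD √11.4 = 3.4, or 30% of the mean;
- six months: mean 6 × 3.8 = 22.8, SD √22.8 = 4.8, or 21% of the mean.

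A centre can look poor over such a window by chance alone.

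**3. Apparent gain with no QRI effect.** Simulation of 20,000 sets of 20 centres: Poisson counts, mean 3.8 per month, gamma-distributed true rates where the coefficient of variation (CV) is above 0. The five lowest centres in the before window are re-observed at unchanged true rates. Result: after/before − 1.

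| Between-centre CV | 3-month windows | 6-month windows |
|---|---|---|
| 0 | 53% | 33% |
| 0.3 | 44% | 23% |
| 0.5 | 40% | 20% |

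The lowest-five rule, the windows and the CVs are assumptions; the protocol states none of them.

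**4. A different selection rule.** Suppose a centre is selected when its before-count is under 60% or under 85% of expected, borrowing the section 9.6 cut-offs. With CV 0, 0.25 or 0.5 and the same windows, the null rise runs from 12% (under 85%, six months, CV 0.5) to 116% (under 60%, three months, CV 0). In one middle case (under 85%, three months, CV 0), 2.53 per month becomes 3.81, a ratio of 1.51. The rise shrinks with longer windows and with more real variation between centres, but stays positive in every scenario.

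**5. A yardstick.** The anticipated participation rise is 40/30 = 1.33. If the flow of eligible patients is constant, that is also a 33% rise in recruits. It lies inside both ranges above.

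**6. Other changes over time.**
- Site opening: at a flat 3.8 per site-month, going from 12 to 20 sites moves the study total from 45.6 to 76.0 per month (ratio 1.67). Going from 17 to 20 moves it from 64.6 to 76.0 (1.18). The rate per active site does not change. Section 7.7 speaks of centres being reviewed as they open, whereas section 9.2 has all sites starting in month 7.
- Calendar: 15 July 2020 is about month 32.4 of 58.9, so (58.9 − 32.4) / 58.9 = 45% of recruitment falls after the telephone/video change. This matters only for windows that straddle mid-2020.
- Downward pressure: section 9.2 implies 24,166 / 71 = 340 prevalent patients per unit against 7,411 / 71 = 104 new ones a year, so using up the prevalent pool could lower later counts. COVID-19 could do the same.

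**The case against.** The case against is substantial, and most of it narrows the point.

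- *Mixed evaluation.* A reader might infer that the QRI is judged by counts alone. Section 7.7.4 says otherwise. Even so, interviews and recordings cannot estimate a change in recruitment; the counts are the only numerical measure of it.
- *Selection.* A reader might infer that all QRI centres are chosen for poor recruitment. Of the first three or four, section 7.7 says "There will be an attempt to ensure these initial centres are as diverse as possible", and section 7.7.4 lists global interventions. The selection argument applies to centre-specific action only.
- *Denominators.* They are not absent. Section 7.7.1 c) has detailed logs with numbers and percentages compared across centres, section 7.7.3 monitors screening logs around interventions, section 9.2 reports the consent percentage monthly, and section 9.6 works per active site-month. What remains is that section 7.7.4 makes denominators optional where the evaluation needs them.
- *The 2020 changes.* A reader might infer that they confound the planned 30% to 40% step. That step is set for month 5 of recruitment, over two years earlier, so they cannot.
- *The yardstick.* Participation among eligible patients and recruits at the weakest centres are different quantities. The 33% is a rough scale only, and the mildest assumptions give less.
- *Analysis detail.* Model specification commonly belongs in an analysis plan, and the pilot objectives do not include estimating the QRI's causal effect. But here the protocol itself names the comparison, and the one it names is weak for centre-specific action.

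**Conclusion.** The point holds in limited form. For centre-specific QRI action, a before/after comparison of counts cannot separate a QRI effect from regression to the mean. With no effect, the apparent gain is about 20% to 53% if the lowest 5 of 20 centres at 3.8 per month are selected, given 3- or 6-month windows and a between-centre CV of 0 to 0.5, all assumed.

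The stronger reading, that a false gain must appear, is not supported. Regression to the mean pushes upward in centres selected for low counts, but COVID-19 and a shrinking prevalent pool may push down, so the net direction is not fixed. The documents also give no basis for extending the point to the trial's endpoints, the recruitment progression criteria or the treatment comparison, none of which uses this evaluation. It is a cheap improvement to a nested study.

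**What to change.** In section 7.7.4:

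1. **Centre-specific interventions.** Replace the before/after count comparison with a Poisson or negative binomial model of monthly randomisations over all active centre-months. Use active site-months as exposure, and include centre effects, calendar time and an indicator that switches on at the recorded intervention date. Centres not yet intervened on then act as concurrent comparators. The low months that prompted action stay in the data but are diluted among the centre's other months; some upward bias may remain and should be acknowledged.
2. **Separate outcomes.** Analyse eligible patients identified per site-month, and the percentage of eligible patients consenting, each in its own right. Do not use eligible patients as an offset: section 7.7.4 lists identifying them as something the QRI may change.
3. **Denominators.** Make the screening log of sections 7.7.1 c) and 9.2 the required source, in place of the optional collection in section 7.7.4.
4. **Global interventions.** Report before/after results as descriptive only. An intervention that reaches all centres together cannot be separated from calendar time.

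The cost is a change of wording and a few hours of analysis. Monthly randomisations by centre and dated interventions are already specified, and the log is already planned. The downside is a wider interval and probably a smaller estimated QRI effect.
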